# Effect of sacubitril/valsartan on sinus rhythm maintenance after catheter ablation in patients with persistent atrial fibrillation without reduced ejection fraction heart failure: a study protocol for a multi-center, open-label, randomized, controlled, superiority clinical trial

**DOI:** 10.3389/fcvm.2024.1303540

**Published:** 2024-01-29

**Keywords:** sacubitril/valsartan, persistent atrial fibrillation, catheter ablation, sinus rhythm maintenance, major adverse cardiovascular events

## Abstract

**Introduction:**

A high recurrence rate of atrial fibrillation was monitored after catheter ablation for persistent atrial fibrillation. Sacubitril/valsartan can improve outcomes for patients with heart failure and ventricular tachycardia, but few studies examined whether it can reduce recurrence or improve cardiovascular outcomes in patients with persistent atrial fibrillation after catheter ablation. In this study, we will assess the effect of sacubitril/valsartan on sinus rhythm maintenance and incidence of major adverse cardiovascular events (MACE) in patients with persistent atrial fibrillation after catheter ablation through a randomized controlled trial (RCT).

**Methods:**

This is a multi-center, randomized, controlled, open-label, superiority clinical trial involving 462 patients without reduced ejection fraction heart failure after catheter ablation of persistent atrial fibrillation. Patients will be randomized to (1) receive the standard treatment strategy plus sacubitril/valsartan titration, or (2) receive the standard treatment strategy without taking sacubitril/valsartan. The primary outcome will be sinus rhythm maintenance rate over 12 months, monitored by random electrocardiogram and 24-h Holter electrocardiogram.

**Discussion:**

This study is designed to evaluate the effect of sacubitril/valsartan on sinus rhythm maintenance and incidence of major adverse cardiovascular events (MACE) in patients with persistent atrial fibrillation after catheter ablation. The results will evaluate sacubitril/valsartan as a novel treatment for improving prognosis and a complement to conventional drug therapy.

**Trial Registration:**

Registered with Chinese Clinical Trials Registry on 27 August 2022, identifier: ChiCTR2200062995.

## Introduction

Atrial fibrillation (AF) now has become a common clinical arrhythmia and refers to the loss of ordered electrical activity in the atria. In China, the available evidence infers that the prevalence of AF in China is 2.32% among people over 65 years old (1–4). The incidence of AF has increased continuously over the past decades, and the rates of hospitalization and fatality are also increasing (5). Based on the duration of AF, AF can be divided into five categories: first diagnosed AF (AF not previously diagnosed), paroxysmal AF (duration < 7 days), persistent AF (duration > 7 days), long-standing persistent AF (duration > 1 year), and permanent AF (diagnosed as AF, patient and doctor have reached an agreement and will no longer attempt to restore sinus rhythm). The sustained onset of atrial fibrillation significantly increases the risk of cardiovascular and cerebrovascular accidents, affecting quality of life and survival of patients. A cohort study showed that the proportion of HF patients with AF is as high as 24.4%, and HF can make further efforts to induce AF (6). Chronic heart failure and persistent atrial fibrillation can promote each other, thus entering a vicious cycle (7, 8).

The therapy of atrial fibrillation has become an increasingly great challenge in the cardiovascular field. Catheter ablation has been confirmed to be an effective way to treat atrial fibrillation, and it has become the most recommended treatment option for symptomatic atrial fibrillation (9). Cochrane systematic reviews have also shown that ablation of persistent AF had a greater advantage in prognosis than anti-arrhythmic drug treatment in eliminating atrial arrhythmias, reducing the need for cardioversion and the risk of hospitalization for cardiac reasons (10). However, the recurrence rate of AF still remained high in patients after catheter ablation, with incidence of early postoperative recurrence (3–12 months) being 25%–40% (11). The CABANA clinical study showed a recurrence rate of 49.9% in the AF ablation group during a long period of follow-up (12). After undergoing catheter ablation, the recurrence rate of persistent AF is higher compared to paroxysmal AF (11). Reducing the recurrence of atrial fibrillation can effectively improve the prognosis of catheter ablation.

Sacubitril/valsartan is the first angiotensin receptor-neprilysin inhibitor (ARNI) with a dual-target inhibitory effect. Studies have shown that AF patients with HF, treated with ARNI, tended to reduce the risk of hospitalization, reversal of cardiac remodeling, and corrected cardiac function after catheter ablation of AF (13–15). However, there is a lack of randomized controlled trials (RCT) to show a therapeutic effect of ARNI in patients with persistent AF after catheter ablation. We will evaluate the effect of ARNI on sinus rhythm maintenance rate and incidence of MACE in patients with persistent AF after catheter ablation in this study through a randomized controlled trial.

## Methods and analysis

### Study design

This prospective trial is a multi-center, randomized, controlled, open-label, superiority trial with a 1:1 ratio of trial and controls. A total of 462 patients with persistent atrial fibrillation after catheter ablation will be recruited in three centers (the First Affiliated Hospital of Shantou University Medical College, Second Affiliated Hospital of Shantou University Medical College, and Jieyang People's Hospital) from August 2022 through August 2025. This protocol is designed according to the Standard Protocol Items: Recommendations for Interventional Trials (SPIRIT) 2013 Statement (16).

### Study hypothesis and objectives

The overall expectation is that patients taking sacubitril/valsartan with persistent atrial fibrillation after catheter ablation will have better sinus rhythm maintenance and cardiovascular outcomes within 12 months than those not taking. This prediction will be tested with the following three objectives. The primary objective will be to evaluate the efficacy of sacubitril/valsartan on sinus rhythm maintenance after ablation of persistent AF patients in this trial. Whether sacubitril/valsartan decreases the incidence of MACE and improves structural indices of the atrium in patients with AF is the secondary objective of this study. The third objective will be to determine the efficacy of sacubitril/valsartan on re-hospitalization rates for cardiovascular causes.

### Population

Patients will be recruited at The First Affiliated Hospital of Shantou University Medical College, The Second Affiliated Hospital of Shantou University Medical College, and Jieyang People's Hospital, three medical centers in Guangdong province. A well-trained research team composed of clinicians familiar with the diagnosis and treatment of atrial fibrillation was set up to screen patients who may meet the research criteria.

### Ethics issues

Ethical approval was obtained before the start of this study from the Committee of Ethics of the First Affiliated Hospital of Shantou University Medical College (Number: B-2022-170-XZ1).

### Inclusion criteria

(1)Adult (age ≥ 18), male or female(2)Physical condition allows oral medication(3)Patients without HFrEF (heart failure with LVEF ≤ 40%)(4)Patients who have a clinical diagnosis of persistent AF (AF lasting >7 days, Holter ECG >24 h will be completed before procedure) and have undergone catheter ablation (successful conversion of rhythm and immediately complete electrocardiogram after procedure)(5)Understand the purpose of the trial and agree to all the study steps, voluntarily sign the informed consents, and be willing to undergo follow-up.

### Exclusion criteria

(1)Pregnant and lactating women(2)Patients with previous ablations (percutaneous or surgical)(3)Acute coronary syndrome (including myocardial infarction), acute stroke, or emergency coronary intervention within 3 months prior to enrollment(4)Heart failure: a clinical diagnosis of heart failure, and transthoracic heart color ultrasound indicates that the left ventricular ejection fraction is 40% or less(5)Patients with acute infectious diseases, important organ injuries, malignant tumors(6)Severe liver insufficiency (Child-Pugh level C) and severe renal insufficiency (eGFR <30 ml/min/L.73 m^2^)(7)The average blood pressure of the three postoperative measurements is lower than 90/60 mmHg(8)Abnormal coagulation mechanism and immune function(9)The subject is currently taking part in another clinical study(10)The investigator considers that the subject is unable to follow the protocol requirements or for any reason considers that the subject is not eligible for the study(11)Allergic to the active ingredient of sacubitril/valsartan or any excipients.

### Withdrawal criteria

Patients can voluntarily withdraw from this clinical trial at any time. Patients who experience the following conditions will also withdraw from the trial:
(1)Serious adverse events (AEs) occurred throughout the entire trial process(2)Unable to continue cooperating with clinical examinations and follow-up due to unexpected reasons.

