### Outcome measurements

#### Primary outcome

The primary endpoint of the study will be the sinus rhythm maintenance rate within 12 months determined by at least the 24-hour Holter electrocardiogram. Patients will be given the Holter electrocardiogram at 3, 6 months and 12 months.

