### Definition

This study differentiate different cardiovascular causes for re-hospitalization into cardioversion, repeat ablation, heart failure, acute coronary syndrome, stroke or transient ischemic attack, or other cardiovascular-related diseases.

MACE are defined as heart failure, myocardial infarction, stroke, malignant arrhythmia and cardiac death. The specific definitions are as follows:
(1)Definition of heart failure: patients who had a history of HF-plausible symptoms, physical examination changes, electrocardiogram changes, cardiac ultrasound changes, and elevated serological markers of heart failure (NT-proBNP > 125 pg/ml or BNP ≥ 35 pg/ml) will be clinically diagnosed as heart failure according to the 2022 AHA/ACC/HFSA Guidelines: Management of Heart Failure. Heart failure with reduced ejection fraction (HFrEF) is classified as an LVEF ≤ 40% (17).(2)Definition of acute coronary syndrome: includes ST-segment elevation myocardial infarction (STEMI), non-ST-segment elevation myocardial infarction (NSTEMI), and unstable angina (UA) according to the guidelines for rapid diagnosis and treatment of acute coronary syndromes in emergency medicine (18).(3)The diagnosis of malignant arrhythmia (MA) refers to the diagnostic criteria for malignant arrhythmia in the 2020 American Heart Association Guidelines for Resuscitation and Emergency Cardiovascular Care (19). MA includes ventricular arrhythmias (ventricular tachycardia and ventricular fibrillation) and grade II or III atrioventricular block. Each type of MA may occur alone or in combination with other types at the same time.

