### Follow-up

After randomization, subjects will have follow-up after 3, 6 and 12 months, mainly in the outpatient clinic according to Figure 2.
(1)The survival status will be confirmed and rehospitalization and occurrence of MACE events will be requested by telephone(2)Holter electrocardiogram (>24 h), transthoracic heart color ultrasound, blood test of blood potassium and kidney function will be performed in the outpatient clinic(3)Adverse event assessment, the main adverse reactions assessed will be: hypotension, high blood potassium, impairment of renal function, as determined in the outpatient clinic(4)Medication consumption in the past will be requested by telephone;(5)Drug bottles will be collected, and the subject reminded of the importance of study medication compliance by the outpatient clinic.

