### Statistical and analytical plans

The statistical analysis will be along with the intention-to-treat (ITT) principles. The ITT population will include patients who meet the criteria, are randomized, and take at least one dose of drugs after being enrolled. For statistical description, continuous variables are described by using mean and standard deviation if they satisfy a normal distribution, skewed distributions are described by medians and quartiles, while categorical variables will be presented as frequency or percentage in each category. For the baselines, the t-test is used to compare the differences for quantitative variable if the data meets the normality test, otherwise, the data will be transformed or rank sum test. Categorical variables such as disease history and smoking history can be tested using chi-square test or rank sum test. For outcomes such as 239sinus rhythm maintenance rate, all-cause death, re-hospitalization rate for cardiovascular causes and MACE, Kaplan-Meier curves will be used to characterize how the probability of an endpoint event changes with survival time, and comparisons between survival curves will be carried out using log-rank tests. We used cox proportional hazards models to estimate hazard ratios and 95% confidence intervals. Cardiac structural function indicators will be described by mean value (±SD) or median and quartiles, and the sphericity of the covariance array will be tested by the Mauchly method. If the data satisfies the sphericity of the covariance array, the analysis of variance with repeated measures data will be used for group comparisons of each indicator. If it is not satisfied, the Greenhouse-Geisser method will be used for comparison of differences. Missing observations will be accounted for using the predictive mean matching (PMM) method. If the missing data is numerical, it will be filled by predictive mean matching; meanwhile if the missing data is non-numerical, logistic regression and discriminant functions will be used to fill it. The *p*-value threshold is 0.05(*p* < 0.05), and when it is below this threshold, indicating that the difference is statistical significant. SPSS statistical software (SPSS Inc, Chicago, IL, USA, version 23) will be used to analyse data.

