### Serious adverse events

Events that are fatal, life-threatening, disabling or incapacitating, or leading to prolonged hospital stay or malformation are defined as serious adverse events in this trial.

The patient blood pressure will be observed by follow-up, and blood samples will be tested for potassium and renal function. The main adverse events will include hypotension, hyperkalemia and renal function impairment that cannot be improved by dose reduction. Adverse reaction criteria: hyperkalemia (blood potassium > 5.5 mmol/L), hypotension (SBP < 90 mmHg or DBP < 60 mmHg), symptomatic hypotension (SBP ≥ 90 mmHg and dizziness, nausea, fatigue, syncope), and creatinine increase more than 50% will be considered as adverse events.

A detailed report will be submitted to the Medicines and Healthcare Products Regulatory Agency in a timely manner when unexpected serious adverse events occur. All patients participating in the trial will receive insurance, including additional healthcare, compensation, or damages. All adverse events which may possibly related to the trial will be recorded in the CRFs.

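### Patients with a serious adverse event must leave the trial, not only the drug, so later rhythm, re-hospitalisation, MACE and death after a non-fatal event would go unobserved

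*Protocol article*

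**What the plan says.** The Withdrawal criteria section first allows voluntary withdrawal and then adds a mandatory rule: "Patients who experience the following conditions will also withdraw from the trial". The first condition is "Serious adverse events (AEs) occurred throughout the entire trial process". The second is being unable to go on with examinations and follow-up. The SAE condition is not limited by relatedness to the drug, by type of event or by arm.

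The Serious adverse events section gives the scope: "Events that are fatal, life-threatening, disabling or incapacitating, or leading to prolonged hospital stay or malformation are defined as serious adverse events". The Definition section says "MACE are defined as heart failure, myocardial infarction, stroke, malignant arrhythmia and cardiac death".

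The outcomes need observation to month 12. Under Primary outcome, "Patients will be given the Holter electrocardiogram at 3, 6 months and 12 months". Under Follow-up, "The survival status will be confirmed and rehospitalization and occurrence of MACE events will be requested by telephone". The analysis section states: "The statistical analysis will be along with the intention-to-treat (ITT) principles". For rhythm, all-cause death, cardiovascular re-hospitalisation and MACE, "Kaplan-Meier curves will be used to characterize how the probability of an endpoint event changes with survival time", with log-rank tests and Cox models. Missing values are to be imputed, by predictive mean matching if numerical and by logistic regression or discriminant functions otherwise.

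**The concern.** The rule removes patients from the study because of an event that is often one of the study's own secondary endpoints. Intention to treat needs outcomes after such an event, and the rule as written gives no way to obtain them. Kaplan-Meier, log-rank and Cox methods assume that a censored patient has the same future risk as those still followed. A patient who has just had a stroke, an infarction or a ventricular arrhythmia is unlikely to meet that assumption for death or re-hospitalisation, and may not meet it for AF recurrence.

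Three things are at stake: the completeness of the death, re-hospitalisation and repeat-event data; the 12-month rhythm and echocardiographic data in the same patients; and the between-arm comparison, if the arms lose such patients at different rates.

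**Working it through.** **Step 1. The sections side by side.**

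- *What is left.* The withdrawal rule names the trial, not the treatment. The companion condition is inability to continue follow-up, so the list treats withdrawal as the end of observation. The Follow-up section describes clinic and telephone contact at 3, 6 and 12 months and says nothing about withdrawn patients.
- *Who leaves.* Most non-fatal infarctions, strokes and ventricular tachycardias or fibrillations are life-threatening, disabling or prolong a hospital stay, and so count as SAEs. Heart failure diagnosed in clinic and grade II atrioventricular block are MACE but need not be SAEs. SAEs that are not MACE also trigger the rule.
- *What is lost.* The triggering event is known and can be counted as a first MACE. After it, AF recurrence, echocardiography, further MACE, re-hospitalisation and death are not observed. A patient who leaves before month 3 has no scheduled Holter at all.

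**Step 2. Size for the primary outcome.** No figure in the plan can be reproduced for this point, because the documents give no SAE rate. From the Sample size section come 42% recurrence at 12 months, a 20% decrease and a risk ratio of 0.46. Since ln(1 - 0.22) / ln(1 - 0.42) = 0.456, the decrease is 20 percentage points. The following are assumptions: SAE share s = 10% or 15% (0.10 × 462 = 46 and 0.15 × 462 = 69 patients); recurrence hazard in SAE patients m = 2 or 3 times that of the others; and the timing of withdrawal.

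Two-class exponential mixture with true recurrence of 42%. The hazard λ per month solves

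(1 - s)e^(-12λ) + s·e^(-12mλ) = 0.58.

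If a fraction f of the high-risk class leaves at month 3, the Kaplan-Meier estimate of 12-month recurrence is

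1 - S(3) × [(1 - s)e^(-12λ) + (1 - f)s·e^(-12mλ)] / [(1 - s)e^(-3λ) + (1 - f)s·e^(-3mλ)],

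where S(3) = (1 - s)e^(-3λ) + s·e^(-3mλ).

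Example with s = 0.10, m = 2, f = 1: λ = 0.04203, S(3) = 0.8711, the ratio is e^(-9λ) = 0.6851, and 1 - 0.8711 × 0.6851 = 0.403.

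If withdrawals are instead spread evenly over 12 months, the high-risk class is multiplied by 1 - f·t/12 at time t, and the observed hazard is integrated from 0 to 12.

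| s | m | Month 3, all leave | Month 3, half leave | Gap | Even, all leave | Even, half leave | Gap |
|---|---|---|---|---|---|---|---|
| 10% | 2 | 40.32% | 41.20% | 0.88 | 40.94% | 41.49% | 0.55 |
| 10% | 3 | 39.50% | 40.80% | 1.30 | 40.45% | 41.24% | 0.79 |
| 15% | 2 | 39.50% | 40.84% | 1.34 | 40.45% | 41.26% | 0.81 |
| 15% | 3 | 38.25% | 40.25% | 2.00 | 39.71% | 40.90% | 1.19 |

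The gap, in percentage points, is the spurious difference when all SAE patients leave in one arm and half in the other, with no true effect. With m = 1 every entry is 42% and the gap is 0.

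**Step 3. Cross-check by a simpler route.** If SAE patients are removed before any rhythm outcome and have relative recurrence risk RR, the observed rate is 0.42 / (1 - s + s·RR). With RR = 2 this is 0.42/1.05 = 0.400 at s = 5% and 0.42/1.10 = 0.382 at s = 10%, a gap of 1.8 points. With RR = 1.5 it is 0.42/1.025 = 0.410 and 0.42/1.05 = 0.400, a gap of 1.0 point. With equal shares in both arms the gap is 0.

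**Step 4. Death, re-hospitalisation and later events.** No model is needed for the direction of the undercount: every such event after a non-fatal SAE withdrawal is missing. Its size cannot be computed, because the documents give no rates.

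**The case against.** *The text does not say that data collection stops, and a journal article condenses the full protocol.* This is true as far as it goes. The end of observation is inferred from leaving the trial, from the companion condition and from the absence of any provision for withdrawn patients. Telephone contact could in principle continue. But the mandatory withdrawal is a stated rule, not an omitted detail, and an analysis plan cannot recover data that were never collected.

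*A reader might infer that every patient with a MACE is lost and that the MACE analysis fails.* The documents do not support that. Some MACE are not SAEs, and the triggering event still counts, so a first-event MACE analysis is largely intact. A first MACE is lost only if an SAE of another kind came earlier.

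*A reader might infer that the rule favours the drug, because serious events caused by sacubitril/valsartan can occur only in the trial group.* Imbalance is possible but not shown. Hypotension, hyperkalaemia and renal impairment can also occur under conventional drugs, and the Interventions section answers hypotension with dose adjustment. If the drug reduces MACE, controls could have more SAE withdrawals. The direction is open.

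*Imputation and the 20% allowance for missed visits already deal with this.* Only in part. The allowance covers lost numbers, not bias. Imputation removes the bias only if the loss depends solely on variables in the imputation model.

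*The effect on the primary outcome is small.* This stands. It is modest against the planned 20 points, and departure of all high-risk patients at month 3 is a harsh assumption.

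**Conclusion.** The point holds in this form: an SAE leads to withdrawal from the trial, treatment discontinuation is not separated from the end of follow-up, and no follow-up after withdrawal is provided. This conflicts with the intention-to-treat principle and makes censoring potentially informative.

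For the primary outcome, recurrence would read about 38-41% instead of 42%, and a spurious between-arm difference of about 0.5-2 points could arise. These figures rest wholly on an assumed 10-15% SAE share and 2-3 times the recurrence hazard. The difference also requires SAE withdrawals to differ by arm. It would be unsound to conclude that the rule could by itself produce or hide the planned effect. The firmer harm is to all-cause death, re-hospitalisation and events after a first non-fatal SAE, which are undercounted by an amount that the documents do not allow one to state. The defect should be fixed, but it does not invalidate the trial.

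**What to change.** 1. Remove SAE from the reasons for withdrawal from the trial.
2. Define discontinuation of study treatment and withdrawal from follow-up as separate events, and record each with its date and reason.
3. Collect rhythm, echocardiography, re-hospitalisation, MACE and vital status to month 12 in all randomised patients unless consent for follow-up is withdrawn. Analyse as randomised.
4. For patients already withdrawn because of an SAE, seek vital status, re-hospitalisation and MACE where consent allows, and report by arm how many could not be recovered.

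Whether the drug is stopped after an SAE is a clinical matter for the clinical team and is not addressed here.

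The cost is amendment wording, approved by the route in the Auditing and amendment section, plus the clinic visits and telephone contacts already scheduled at 3, 6 and 12 months. The Trial status section describes the trial as recruiting, and missed follow-up is often irrecoverable, so an early change saves more data than a late one.
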